## Abstract

**Introduction:**

The choice of trigger drug for the controlled ovarian hyperstimulation (COH) protocol correlates with the outcome of *in vitro* fertilization/intracytoplasmic sperm injection embryo transfer (IVF/ICSI-ET). The co-administration of gonadotropin releasing hormone agonist (GnRH-a) and human chorionic gonadotropin (hCG), i.e., dual trigger, for final oocyte maturation, has received much attention in recent years. This trial was designed to determine whether a dual trigger approach by lengthening the time between trigger and ovum pick-up (OPU) improves the quantity and quality of mature oocytes/top-quality embryos and pregnancy outcomes in expected normal responders with a high immature oocyte rate.

**Methods and Analysis:**

We propose a study at the Affiliated Hospital of Shandong University of Chinese Medicine. A total of 90 individuals undergoing COH use a fixed GnRH antagonist protocol. They will be assigned randomly into two groups according to the trigger method and timing: recombinant hCG (6500 IU) will be injected only 36 hours before OPU for final oocyte maturation (hCG-only trigger); co-administration of GnRH-a and hCG for final oocyte maturation, 40 and 34 hours prior to OPU, respectively (Dual trigger). The primary outcome is metaphase-II (MII) oocytes rate. Secondary outcomes are number of oocytes retrieved, fertilization rate, top-quality embryos rate, blastula formation rate, embryo implantation rate, clinical pregnancy rate, miscarriage rate, live birth rate, cumulative pregnancy/live birth rates, and ovarian hyperstimulation syndrome (OHSS) rate.

**Ethics and Dissemination:**

The reproductive ethics committee of the Affiliated Hospital of Shandong University of Traditional Chinese Medicine certified this study (Identifier: SDUTCM/2021.7.26) as ethical. All individuals will sign written informed consent. All data and biological samples will be protected according to law. The results of this study will be disseminated in a peer-reviewed scientific journal.

**Clinical Trial Registration:**

[chictr.gov.cn], identifier [ChiCTR2100049292].

## Highlights

1.This is the first randomized controlled trial comparing hCG-only trigger and dual trigger (co-administration of GnRH-a and hCG, 40 and 34 hours prior to OPU, respectively) among normal ovarian responders with ≥ 50% immature oocytes in a previous IVF cycle triggered with hCG.

2.A prospective, randomized, superiority, parallel, controlled study aims to determine if co-administration of GnRH-a and standard dosage hCG trigger optimizes oocyte maturation, embryo quality, and pregnancy outcomes in normal responders when compared to hCG-only trigger.

3.Our findings will shed new light on IVF trigger approaches for infertile women with high immature oocyte rates.

## Introduction

At the moment, IVF/ICSI-ET is one of the most widely used techniques for addressing infertility. In order to obtain the ideal number and quality of oocytes, COH program came into being. hCG is usually used as a substitute for endogenous luteinizing hormone (LH) surge at the end of COH to induce follicular maturation and the continuation of meiosis. Nonetheless, because of the prolonged luteinization, using hCG alone as a trigger raises the risk of OHSS (1).. With the steady expansion of GnRH antagonist (GnRH-ant) use in clinical practice, a growing number of reproductive specialists are recommending GnRH-a as trigger medicines. GnRH-ant binding to the pituitary GnRH receptor is reversible. After GnRH-a injection, the receptor can dissociate from GnRH-ant and be activated by GnRH-a, allowing the acute release of endogenous LH and follicle stimulating hormone (FSH), i.e., flare up action. In comparison to spontaneous ovulation, the total quantity of endogenous gonadotropins (Gn) generated by GnRH-a triggering is lower and of shorter duration, which may contribute to the lower risk of OHSS. Nevertheless, GnRH-a triggers decreased pregnancy and live birth rates in fresh embryo transfer cycles, as well as higher risks of early miscarriage, requiring considerable luteal phase support (2, 3).

Given that fresh embryo transfer is the preferred option of assisted reproduction, oocyte maturation and ovulation induction by co-administration of GnRH-a and hCG, the dual trigger, have attracted much attention recently. In terms of number of oocytes retrieved, number of MII oocytes, fertilisation rate, top-quality embryos rate, and embryo implantation rate, a meta-analysis found that dual trigger was more advantageous but not statistically different from hCG trigger (4). Dual trigger is available in two ways (5, 6): Concomitant use GnRH-a and low-dose hCG (1000-2500 IU) as trigger drugs 35-37 hours prior to OPU reduces the risk of OHSS in high responders (7). And it can compensate for luteal insufficiency in GnRH-a trigger, which is associated with comparable or even higher pregnancy rates than hCG trigger (6–8)]. Furthermore, combining low-dose hCG with GnRH-a (dual trigger) to induce final oocyte maturation improved the number of oocyte retrieval in poor responders without raising the risk of clinically severe OHSS (9). Another alternative dual trigger approach is co-administration of GnRH-a and hCG for final oocyte maturation, 40 and 34 hours prior to OPU, respectively. Beck-Fruchter R et al. used this trigger to prolong the period between trigger and OPU to successfully obtain mature oocytes and achieve pregnancy, delivery in a patient with empty follicle syndrome (EFS) (10). According to recent findings, normal responders who had a lower rate of mature oocytes (less than 50%) shown a significant increase in the number of oocytes and transferable embryos obtained with this dual trigger method, as well as in the proportion of oocytes obtained to the number of preovulatory follicles, but the pregnancy rates were not conclusive (11, 12). Co-administration of GnRH-a and hCG 40 and 34 hours prior to OPU may therefore be considered novel therapeutic options for patients with poor mature oocyte rates. Additionally, Haas J et al. discovered that decreased conexin43 expression, in combination with enhanced epiregulin and amphiregulin expression, in the GCs of patients undergoing dual trigger may account for the better oocyte and embryo quality (13).

Although the results showed some benefit in terms of number of oocytes retrieved and MII oocytes using dual trigger in a prospective study involving all IVF/ICSI patients, there was no statistical difference. As a result, the population for whom the dual trigger strategy would be appropriate should be clarified further (14). Dual trigger has been shown to enhance oocyte maturation and improve top-quality embryo, pregnancy, and live birth rates in individuals with ovarian hypo-responsiveness (15, 16). Furthermore, a recent meta-analysis by Orvieto R shown that dual trigger increased the number of oocytes retrieved, the number of MII oocytes retrieved, and the number of high-quality embryos obtained in patients with poor maturation rates after prior hCG trigger cycles (7). In normal ovarian responders, the findings revealed that using GnRH-a and hCG simultaneously (dual trigger) substantially improved oocyte maturation in patients with poor oocyte maturation rates in hCG trigger cycles (17). Similar results were obtained in the study by Fabris AM and his colleagues (18). This suggests that when the oocyte maturation rate following a standard hCG trigger is less than 50%, the way GnRH-a combined with hCG to ultimately induce oocyte maturation should be considered in the next COH cycle. Nevertheless, there is increasing evidence, albeit in part controversial, that a dual trigger approach using both GnRH-a and hCG increases the number of MII oocytes, 2PN zygotes, transferable embryos, and pregnancy rates in normal ovarian responders (19–23). Yet, in individuals who have had a previous hCG trigger cycle, the benefit of trigger method utilizing GnRH-a and standard dosage hCG 40 and 34 hours prior to OPU, respectively, on oocyte retrieval, MII oocyte, transferrable embryo, and other reproductive outcomes remains unknown.

Trigger methods are related to the number of oocytes retrieved, mature oocytes, 2PN fertilisation rate, number of top-quality embryos, embryo implantation rate, clinical pregnancy rate, miscarriage rate, ongoing pregnancy rate, live birth rate, etc. The acquisition of mature oocytes is required prior to initiating IVF-ET. Obtaining higher-quality embryos is critical for IVF-ET success. The ultimate aim of IVF-ET is to maintain pregnancy and deliver a live baby. Therefore, a comprehensive evaluation of the patient situation and individualized formulation of the appropriate trigger method and trigger dosage are necessary. Previous studies have been compromised by sample size, data statistics, or technique, and debate has persisted about the study’s conclusions. The study is a prospective randomized superiority parallel controlled trial, we aimed to investigate whether co-administration of GnRH-a and standard dose hCG trigger could improve oocyte maturation, embryo quality and pregnancy outcomes in normal responders with poor oocyte maturation rates by prolonging the time between trigger and oocyte retrieval.

## Methods and Analysis

### Study Design

The study is a prospective, randomized, superiority, parallel, controlled trial. Enrolment of patients with normal ovarian response undergoing IVF/ICSI is expected to begin in July 2021 and continue until July 2023 at the reproductive centre of integrative medicine, the affiliated hospital of Shandong University of Traditional Chinese Medicine. We adhered to the SPIRIT recommendations when drafting this protocol (24). The flow chart for this study is shown in **Figure 1**, and the study process schedule is shown in **Table 1**.

**Figure 1 f1:**
[figure not shown]
Flowchart showing the study process.

**Table 1 T1:** Overview of study visits.

	Enrolment Baseline	COH phase	hCG trigger	Dual trigger	Three days after OPU	Embryo transfer	Pregnancy testing	Follow-up 1 year
Information and counselling	X							
Signing of informed consent	X							
Treatment related data collection		X	X	X	X	X	X	X
Randomization			X	X	X	X		
Transvaginal ultrasound scan	X							X
Ovarian morphology UL scan	X	X	X	X	X	X		
Blood sample	X	X	X	X	X	X	X	

### Eligibility Criteria

#### Inclusion Criteria

(1) Expected normal ovarian responder (NOR): 6 ≤ antral follicle counting (AFC) ≤ 15; 1.2 ng/ml ≤ anti müllerian hormone (AMH) ≤ 3.5 ng/ml; basal FSH< 10 mIU/ml; no previous history of cancellation of IVF cycles with low or high ovarian response; (2) Patients with ≥ 50% immature oocytes in the only one previous fresh IVF cycle triggered with hCG; (3) In the previous IVF cycle, standard ovarian stimulation protocol was performed using a GnRH-ant protocol and triggered when two follicles were ≥ 18mm in diameter. 

#### Exclusion Criteria

(1) Age ≥ 40 years; (2) body mass index (BMI) ≥ 30 kg/m^2^; (3) Individuals with severe OHSS during ovarian stimulation; (4) Patients with endocrine disorders (diabetes, hyperprolactinemia, hypothyroidism, congenital adrenal hyperplasia, Cushing’s syndrome or polycystic ovary syndrome); (5) Untreated moderate and severe endometriosis, submucosal myoma, multiple endometrial polyps, pelvic inflammation, uterine malformation, Asherman syndrome and hydrosalpinx; (6) Patients with abnormal immune function and chromosome karyotype of both spouses.

#### Dropout Criteria

Participants who do not fulfil the inclusion criteria, do not adhere to standard treatment procedures, or refuse to sign an informed consent form as a result of a departure from the clinical trial protocol should be eliminated after enrolment. Participants that fulfilled the inclusion criteria but were dislodged from the clinical trial for various reasons, including two instances when the subject withdrew on their own and when the investigator noticed the subject had withdrawn.

### Study Case Discontinuation

Subjects in the study who experience serious adverse reactions, special physiological reactions, other unexpected events, or who are not suitable to continue participating in the trial will be terminated from the trial. Urgent measures will be taken during the study if the subject has a serious complication or if the condition worsens.

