### Randomization and Blinding

On the trigger day, randomization will begin. Individuals will be assigned to one of two groups, A or B, in a 1:1 ratio by computer, using a random sequence of codes in the order of enrolment. The randomization scheme was entered into an online central randomization database (www.medresman.org). A dedicated data specialist will run the online randomization procedure, who will not be involved in patient recruiting or clinical care. The doctors will be notified of the allocation results *via* email after randomization. Allocation concealment will be guaranteed since the service will not divulge the allocation until after the randomization process, i.e. after the baseline visit. Due to the nature of the intervention, we will not blind the patients and doctors on the assigned groups. However, the trial outcome assessors will be blinded to the intervention.

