### Reproductive Outcomes

The primary outcome is MII oocytes rate (percentage of the number of mature oocytes to the number of oocytes retrieved).

The secondary outcomes are number of oocytes retrieved, fertilization rate (the proportion of oocytes that become fertilized), top quality embryos (TQE) rate (percentage of the number of TQE to total embryos obtained), blastula formation rate, embryo implantation rate (percentage of the number of gestational sac to the total transferred embryos), clinical pregnancy rate (percentage of participants with clinical pregnancy), miscarriage rate (percentage of participants with loss of a diagnosed clinical pregnancy before 12 weeks gestation), live birth rate (the proportion of a delivery of one or more living infants), cumulative pregnancy/live birth rates (percentage of participants with clinical pregnancy/live birth after one year of follow-up), severe OHSS rate (percentage of participants with OHSS). TQE was defined as seven or more blastomeres on day three, evenly sized blastomeres, and less than 20% fragmentation, whereas low quality embryos were characterized as anything else. On transvaginal ultrasonography, clinical pregnancy was defined as the appearance of a gestational sac and foetal heartbeat.

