### Data Statistical Analysis

All randomized individuals will be included in the analysis of the primary trial end point (intention-to-treat analysis). For analyses of other outcome variables, only subjects randomized to the study protocol will be included (per-protocol analysis). SPSS version 26.0 and R statistical package version 4.0.0 will be used to analyse all the data. The continuous data will be normalized using the two independent samples t-test and presented as mean ± standard deviation (Mean ± SD). If the distribution is not normal, use nonparametric tests, which are expressed as the median (interquartile range) [M (IQR)]. Categorical data will be presented as frequency (percentage) [n (%)] using chi square test and Fisher’s exact test for expected frequencies less than five. P < 0.05 indicates that the difference is statistically significant.

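### The discontinuation rule ends trial participation on open grounds without preserving outcome follow-up, so randomised women can drop out of the pregnancy and live birth comparisons for reasons the trigger affects

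*Protocol article*

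**What the plan says.** All references are to the Protocol article.

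- **Study Case Discontinuation.** After serious adverse reactions and special physiological reactions, the list of grounds ends with "other unexpected events, or who are not suitable to continue participating in the trial will be terminated from the trial". The rule is mandatory. It does not define suitability or name who judges it, and it does not say whether outcomes are still collected. The next sentence concerns urgent measures for complications.
- **Randomization and Blinding.** "On the trigger day, randomization will begin", and "we will not blind the patients and doctors on the assigned groups". Outcome assessors are blinded.
- **Reproductive Outcomes.** The denominators are per woman: "clinical pregnancy rate (percentage of participants with clinical pregnancy", and for the cumulative rates "percentage of participants with clinical pregnancy/live birth after one year of follow-up".
- **Table 1 (Overview of study visits).** Treatment-related data collection runs through to the column "Follow-up 1 year".
- **Data Statistical Analysis.** For the MII rate, "All randomized individuals will be included in the analysis of the primary trial end point (intention-to-treat analysis"). For every other outcome, "only subjects randomized to the study protocol will be included (per-protocol analysis").
- **Dropout Criteria.** A separate rule eliminates women after enrolment for ineligibility, non-adherence or missing consent, and also describes withdrawal.

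**The concern.** The randomised treatment is a trigger that is complete before oocyte retrieval. Retrieval, fertilisation, embryos, pregnancy and live birth all follow randomisation, and the trigger is meant to influence each of them. A rule that ends participation on open grounds, applied by doctors who know the arm, can therefore remove women for reasons connected with the result. Blinded assessors cannot recover outcomes for women who are no longer followed.

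There are two routes. A woman with a complication after retrieval or in early pregnancy may be terminated, and any later frozen transfer within the year then goes uncounted. A woman with no mature oocytes, no fertilisation or no transferable embryo might be judged unable to continue, although for pregnancy and live birth she is a known failure. If the second kind of removal is commoner in the arm with poorer maturity, the women who remain are selected for having embryos and the comparison moves toward no difference.

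**Working it through.** **1. The plan's own figure.** Inputs from Sample Size Estimation: MII rate 40% (hCG-only) and 70% (dual), SD 40%, two-sided α 0.05, power 90%.

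- Normal approximation: n = 2(1.960 + 1.282)² × 40² / 30² = 37.4, so 38 per group.
- The t-test version gives 38.3, so 39. Dividing by a rank-test efficiency of 0.955 gives 40.2.
- Dropout: 40 / 0.90 = 44.4, so 45 per group and 90 in total.

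The stated 40, 45 and 90 are reproduced, and nothing in this point changes them.

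**2. How termination becomes exclusion.** Read in order, the sections give this chain:

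- Women are randomised on the trigger day.
- Unblinded doctors may find a woman unsuitable at any later time, and she is then terminated.
- Intention-to-treat is reserved for the MII rate, and the pregnancy and live birth outcomes carry the per-protocol label.
- No section counts a terminated woman as not pregnant. The section on adverse events follows only serious adverse events to resolution.

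The per-participant definitions and the one-year column in Table 1 imply the opposite, so the sections do not agree.

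**3. Size on simple assumptions.** The documents give no pregnancy rate and no rate of women without a usable embryo, so all rates here are assumed. Let p be the pregnancy rate in women with a usable embryo (equal in both arms), f the fraction without one, and r the share of those women who are removed.

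Rate per randomised woman = p(1 − f). Rate after removal = p(1 − f) / (1 − r f).

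With p = 50%, f = 20% (hCG-only) and 5% (dual):

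| Women without an embryo removed | hCG-only | Dual | Difference |
|---|---|---|---|
| None | 0.5 × 0.80 = 40.0% | 0.5 × 0.95 = 47.5% | 7.5 points |
| Half | 0.400 / 0.900 = 44.4% | 0.475 / 0.975 = 48.7% | 4.3 points |
| All | 0.400 / 0.800 = 50% | 0.475 / 0.950 = 50% | 0 |

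With p from 40% to 60% and f from 10%/5% to 30%/10%, the difference per randomised woman is 2 to 12 points. It is 0 after full removal in every case.

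A count of the planned size, with the 10% dropout allowance used up (9 of 90): 18/45 (40.0%) versus 22/45 (48.9%) is 8.9 points. Removing 7 hCG-only and 2 dual-trigger women without embryos gives 18/38 (47.4%) versus 22/43 (51.2%), or 3.8 points.

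**4. Size from the planning figures, as a worst case.** Assume that each woman's maturity rate follows a beta distribution with the planning mean m and SD s, that 8 or 10 oocytes are retrieved, and that live birth is 40% in women with at least one mature oocyte.

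- k = m(1 − m)/s² − 1, a = mk, b = (1 − m)k, and P(no mature oocyte) = B(a, b + n)/B(a, b), where n is the number of oocytes.
- m = 0.40, s = 0.40: k = 0.5, a = 0.20, b = 0.30, P = 0.392 (8 oocytes) and 0.375 (10).
- m = 0.70, s = 0.40: k = 0.3125, a = 0.219, b = 0.094, P = 0.180 and 0.171.
- Live birth per randomised woman, 8 oocytes: 0.40 × 0.608 = 24.3% versus 0.40 × 0.820 = 32.8%, difference 8.5 points.
- Half removed: 0.243 / 0.804 = 30.2% versus 0.328 / 0.910 = 36.0%, difference 5.8 points, so about a third of the gap is lost.
- All removed: 40% versus 40%.

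The result depends heavily on the SD. At SD 25% the fractions with no mature oocyte are about 12–14% versus 2%, and the true difference is 4–5 points. At SD 20% they are about 7–9% versus 1%, and 2–3 points.

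**The case against.** The strongest reply is that the section is mainly a safety provision. It starts from serious adverse reactions and goes on to urgent measures. Nowhere does it say that a woman without mature oocytes or embryos is terminated. Poor maturity is hardly unexpected here, since entry requires at least 50% immature oocytes in the previous cycle and the planning rate on hCG alone is 40%. A reader might infer that such women will be removed. The documents do not support that; the open wording only allows it.

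A reader might also infer that termination after a one-off trigger can only mean that outcome collection stops. That does not follow. Blood samples and visits continue after retrieval, and termination could mean stopping those. Consent precedes stimulation, so the rule may also act before randomisation, where it cannot bias the comparison. The per-participant definitions and Table 1 suggest that outcomes are meant to be counted for everyone.

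The exclusion itself comes from the per-protocol label in Data Statistical Analysis, so rewording the discontinuation rule alone would not be enough. That label sits on words that literally describe randomised subjects, so it too needs clarifying.

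The illustrations in steps 3 and 4 assume equal pregnancy or live birth rates among women with usable embryos or oocytes. The trial hopes the trigger also improves embryo quality, in which case part of the difference would survive. These secondary comparisons are weak in any case: at 28% versus 36%, 45 per arm gives about 12.5% power.

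All of this limits the size and certainty of the point. What it does not answer is that a mandatory rule, as printed, ends participation of randomised women on undefined grounds and nowhere preserves their outcomes. That is something the article states, not detail left to a fuller document. Correcting the analysis set later cannot restore data that were never collected.

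**Conclusion.** The point holds as a gap in the stated rule, not as a prediction of what the site will do. Randomised women can leave the pregnancy, live birth and one-year cumulative comparisons for reasons related to the trigger's result or its complications, and this conflicts with the per-participant definitions.

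If women without mature oocytes or transferable embryos were among those removed, the secondary differences would be diluted. On the assumed rates, half removal cuts 7.5 points to 4.3, or 8.5 to 5.8 on the planning-figure model. A reader might conclude that a real difference would be erased. That needs removal of all such women and a benefit acting wholly through having usable oocytes or embryos, and the documents establish neither. For removals after complications, the documents give nothing from which to fix a direction or size.

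The primary MII rate is largely unaffected. It is declared intention-to-treat and is known at retrieval, before anyone could be removed for lacking mature oocytes. The sample size stands.

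**What to change.** In Study Case Discontinuation, separate the two meanings of termination:

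- Trial procedures may be stopped, but retrieval, embryo, transfer, pregnancy, live birth and adverse event data are collected for every randomised woman to the end of the one-year follow-up, unless she withdraws consent for data collection.
- Having no mature oocytes, no fertilisation or no transferable embryo counts as no pregnancy and no live birth from that retrieval, and is not a ground for ending follow-up.

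Then reconcile Dropout Criteria and Data Statistical Analysis with this, so that pregnancy and live birth are analysed per randomised woman, as the outcome definitions already imply. Any per-protocol analysis of these outcomes can be kept as supportive.

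The clinical handling of complications is unchanged. The cost is a wording amendment and a few more follow-up contacts among 90 women at one centre.
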